We propose a randomized, controlled trial to evaluate the effectiveness of an mHealth diabetes adherence support intervention delivered by clinical pharmacists and health coaches. We will randomize 220 patients through UI Health to either: (1) mHealth diabetes adherence support through clinical pharmacists and health coaches; or (2) usual care. After one year, patients completing the mHealth intervention will be monitored for an additional year while the usual care group receives the mHealth approach. Outcomes include medication adherence, hemoglobin A1c, blood pressure, and LDL-cholesterol levels. The specific aims include: (1) evaluate the effectiveness of an mHealth diabetes adherence support intervention delivered by clinical pharmacists and health coaches to African-American and Latino adults with uncontrolled type 2 diabetes; (2) evaluate the maintenance of improved diabetes behaviors as well as clinical outcomes one year after completing the intervention; (3) evaluate the cost and cost-effectiveness of mHealth diabetes adherence support compared to usual care; and (4) evaluate the reach, adoption, and implementation of mHealth diabetes adherence support based on the RE-AIM framework.

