#### Crossover Transition

1. One year after enrollment, the participants receiving *mDAS* will have the intervention components phased out to assess maintenance. The participants in the usual care group during year 1 will receive *mDAS* support for the subsequent year to assess intensification.
2. Coaches will help participants enlist social support and community resources for long term assistance with medications.

3. Coaches may periodically be contacted by disengaged participants during the following year. These communications will be logged.

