### **Transition and Retention**

Despite having "access" to healthcare, participants will be economically vulnerable individuals with uncontrolled diabetes. Ethically, we acknowledge that the "usual care" currently received often does not meet patients' needs or standards of care. Therefore, participants assigned to usual care will receive initial support to engage existing resources available through UI Health, such that healthcare providers will consider this an acceptable alternative upon randomization (clinical equipoise).

Upon randomization, participants will receive referrals to a diabetes educator and clinical pharmacist for medication reconciliation, adherence support, and education. Staff can schedule the visit at data collection. This is important as our prior work with medication reconciliation identified discrepancies in almost 60% of patients. A one-page list of clinic resources with names and direct telephone numbers (e.g., social worker) will be provided so they can more easily navigate the system. Finally, low-literacy, paper-based diabetes education information will be provided. At the end of year 1, these patients will cross-over and receive *mDAS*. Prior to this transition, HCs will work with the patients and their social support network to prepare them for the transition. Participants randomized to usual care will receive *mDAS* for one year.

*Retention strategies.* Participants will be reimbursed \$30 for each data collection. Participants assigned to the intervention in year one will receive an additional \$50 at 6 months and 12 months if they complete at least one videoconference before each data collection. Participants assigned to the intervention in year two will receive an additional \$50 at 18 months and 24 months if they complete at least one videoconference before each data collection. Participants who complete all five data collection visits and videoconferences with the pharmacist as described above will receive up to \$250 for completing the study.

*Additional Retention Strategies for mDAS Sleep Sub-study Supplement* Participants will be reimbursed an additional \$40 for participating in the sleep sub-study and turning in the wrist actigraph.

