Cost and Healthcare Utilization Data: We will conduct a cost-utility analysis comparing *mDAS* with usual care, following the guidelines for conducting pharmacoeconomic analyses by the Panel on Cost-Effectiveness and Medicine and the International Society for Pharmacoeconomics and Outcomes Research. We will conduct the analysis from the health-system perspective, and include the costs of running the program as well as the costs associated with patient health services utilization. Costs will include pharmacists and HCs (training and implementation), educational materials, tablet computers with data service, text messaging, and videoconferencing. Health services utilization will include costs associated with hospital admissions, emergency room visits, outpatient visits and prescription medications during the intervention period. Participants will be followed throughout the study to obtain data on their programmatic and healthcare services related costs. At data collection points, research assistants will obtain the necessary information from patients on healthcare use outside of UI Health. We will capture UI Health care information electronically from the hospital electronic records and billing data for enrolled subjects. We have previously analyzed similar UI Health data. Additional costs (salaries for HCs, etc.) will be estimated from prevailing internal costs at the time. Cost estimations for healthcare use will be based on national Medicare reimbursement rates (average DRG rates) for hospitalization, Medicare fee schedules for physician and other professional services, and Medicare's Resource-Based Relative Value Scale for outpatient procedures. Since our study will span a period exceeding one year, appropriate costs will be discounted and adjusted for inflation.

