### Cost and Cost Effectiveness

We will obtain program and healthcare use data to estimate the cumulative costs from a health system perspective for each group over 24 months. To accommodate drop-outs and missing data (censoring) in the cost estimates, we will use a modification of survival analysis. To estimate average cumulative costs, we will divide the time interval following randomization into months, and then estimate cumulative costs to time  $T$  (i.e., 6, 12, 18, and 24 months) as:  $C_{(T)} = p_t \times c_t$ , where  $p_t$  is the probability of participating at month  $t$ , and  $c_t$  is the mean cost at month  $t$  given participation at  $t$ . Patients participating at the end of follow-up contribute cost information from randomization to end of follow-up, while patients who drop out contribute costs from randomization through drop-out date (and then zero costs thereafter until end of subject follow-up). We will then discount to estimate the average present value of costs:  $C_{(T)} = \sum_{t=1}^T \hat{S}_t \bar{C}(t) / (1 + r)^{t-1}$ , where  $r$  is the discount rate and  $\hat{S}_t$  is the Kaplan-Meier estimator of the probability of participation to month  $t$ . We will use a discount rate of 3% per year and calculate  $C_{(T)}$  for subjects in both groups. For the cost-effectiveness analysis, we will calculate the incremental average costs resulting from *mDAS* vs. usual care and compare via a two-sample  $t$ -test for independent groups. Costs may not be normally distributed; however, if the sample is sufficiently large,  $t$ -tests on untransformed costs are appropriate.

Our effectiveness measures will include improvements in A1c, blood pressure, of cholesterol levels and projected quality-adjusted life-years (QALYs). Furthermore, a reduction in unnecessary healthcare utilization (emergency room visits and preventable hospitalizations) may result in cost savings. The incremental cost-effectiveness ratio (e.g., cost per change in A1c) of *mDAS* vs. usual care will be estimated at the end of 12 and 24 months. Cost per QALY will be determined from projections of continued mHealth involvement and assumptions concerning

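### The 24-month cost-effectiveness ratio is labelled mDAS versus usual care, but the usual-care arm receives mDAS in Year 2, so it compares immediate with delayed mDAS

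*Protocol*

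**What the plan says.** Section 12.0, Cost and Cost Effectiveness, estimates "cumulative costs from a health system perspective for each group over 24 months" and compares average costs between the two groups with a two-sample t-test. It then fixes the result to be reported: an incremental ratio, with cost per A1c change as the example, which for mDAS "vs. usual care will be estimated at the end of 12 and 24 months". Aim 3 in Section 3.0 is the cost and cost-effectiveness of mDAS compared with usual care.

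The design changes both arms' treatment at month 12. Under Transition and Retention, the protocol says of the usual-care patients: "At the end of year 1, these patients will cross-over and receive" mDAS, for one year. Under Crossover Transition (Section 6.1), participants who had mDAS first "will have the intervention components phased out to assess maintenance". Section 1.0 describes the second year in the same way: the first arm is "monitored for an additional year while the usual care group receives the mHealth approach".

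On the data side, Section 8.0, Cost and Healthcare Utilization Data, counts "costs associated with hospital admissions, emergency room visits, outpatient visits and prescription medications during the intervention period".

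**The concern.** The ratio is named for a comparison that exists only up to month 12. After that the arm called usual care is receiving mDAS, and the arm called mDAS has returned to usual care. A 24-month difference between the randomised groups therefore measures having the programme a year earlier, not having it at all. The cost section does not say how Year 2 is handled.

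The protocol itself fixes the horizon, the label and the between-group comparison, so this is not a detail left to a later analysis plan. What is at stake is one named output of Aim 3. Section 12.0, Sustainability, intends the cost-effectiveness data to help guide resourcing after the study, so a reader could take a 24-month figure at its label.

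**Working it through.** The protocol gives no cost-effectiveness figure to reproduce. The check builds the 24-month contrast from the plan's own inputs.

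**Inputs from the protocol**
- Sample Size Justification: A1c effect E = 1.0 point, SD 1.8, cross-time correlation 0.30, design effect 1.34, 20% dropout, N = 220.
- Cost and Cost Effectiveness: discount rate 3% per year; costs summed by month since randomisation and weighted by participation.
- Sustainability: only a limited loss of benefit is expected after mDAS ends, with no figure.

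**Assumptions**
- The mDAS effect after one year is the same in both arms.
- A share m of it remains one year after mDAS ends (range shown).
- A1c is read at the time point, not accumulated.
- Programme cost is one unit per month assigned to mDAS.
- Dropout, where used, is spread over 24 months as S(t) = 0.8^(t/24).

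**Treatment by period**

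| Arm | Months 1-12 | Months 13-24 |
|---|---|---|
| mDAS first | mDAS | usual care |
| Usual care first | usual care | mDAS |

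**Denominator.** Let the advantage be the A1c reduction in the first arm minus that in the second.
- Month 12: E - 0 = 1.0.
- Month 24: mE - E = -(1 - m) × 1.0.

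**Precision.** Effective size per arm = 220 × 0.8 / 1.34 / 2 = 65.7.
- Post values: SE = 1.8 × √(2/65.7) = 0.31.
- Change scores: SD = 1.8 × √(2 × (1 - 0.30)) = 2.13, so SE = 0.37.

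Normal probabilities that the estimated denominator is zero or negative at month 24:

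| m | Expected advantage | Post values | Change scores |
|---|---|---|---|
| 1.00 | 0 | 50% | 50% |
| 0.90 | -0.10 | 62.5% | 60.6% |
| 0.75 | -0.25 | 78.7% | 74.9% |
| 0.50 | -0.50 | 94.4% | 91.1% |

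At month 12 the same probabilities are 0.07% and 0.4%.

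**Numerator, programme cost only.** Each month is weighted by 1.03^(-(t-1)/12), and by S(t) where dropout applies.
- No dropout: first arm (months 1-12) 11.84 units; second arm (months 13-24) 11.49. The increment is 0.34 from unrounded sums, and 0.34 / 11.84 = 2.9% of the 12-month increment.
- 20% dropout: 11.15 against 9.69. The increment is 1.47 from unrounded sums, and 1.47 / 11.15 = 13%.

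What is left of the increment comes from timing and attrition, not from mDAS against no mDAS. The annual rate was converted to months here. The printed formula has t - 1 as its exponent with t in months. Taken literally at 3% per month, it would give about 30% and 37%, but the text states 3% per year.

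**The case against.** The strongest reply is that Aim 3 can still be answered. The same sentence plans a 12-month ratio, which is a clean randomised comparison, and the crossover is stated openly throughout the protocol. Immediate versus delayed mDAS over 24 months is also a legitimate question for a health system. All of this stands. It means the remedy is to restrict or relabel one of two time points; it does not make the 24-month label correct.

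Nothing elsewhere in the protocol repairs the label. The carry-over and period terms under Primary Outcomes belong to the outcome models and are not applied to costs. The projections in the cost section concern cost per QALY, not the 24-month cost per change in A1c.

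Three stronger readings are tempting and are not supported:

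- **That mDAS will appear harmful at 24 months.** The wrong sign depends on the retained share, on equal effects in both arms and on A1c read at month 24. If the effect were accumulated over 24 months, with linear onset and decline, the early arm would lead by (1 + m)/2, that is 0.5 to 1.0 A1c-point-years. The sign would then be right, though the contrast would still be early against late mDAS. Nor can the whole ratio be called zero over zero. Admissions, emergency visits, outpatient visits and prescriptions also enter the numerator and need not cancel.
- **That the bootstrap acceptability curve is wrong too.** It is built on the cost-utility ratio, whose QALYs are projected with a Markov model. The protocol does not say that the 24-month A1c ratio feeds it. What stays open is whether 24-month arm totals enter its net costs.
- **That utilisation is counted in different calendar years by arm.** The phrase about the intervention period in Section 8.0 could be read that way. The same paragraph follows participants throughout the study, and the cost section counts months since randomisation in both groups. This is loose wording, not a conflict.

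**Conclusion.** The 24-month mDAS-versus-usual-care ratio is wrong as written. That both arms have been assigned a year of mDAS by month 24 follows from the text and needs no assumption.

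The size is conditional. Given an equal 1.0-point effect in each arm's mDAS year and A1c read at month 24, the plan's own expectation of limited decline puts the denominator at or just below zero. The programme-cost increment is about 3% to 13% of its 12-month value, depending on dropout. Utilisation costs are outside this illustration. Under those conditions the ratio would be unstable or of the wrong sign even if mDAS works as planned.

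The 12-month ratio and the Aim 1 analyses are not affected.

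**What to change.** In Section 12.0, Cost and Cost Effectiveness:

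1. Limit the within-trial cost comparison and cost-per-outcome ratio of mDAS versus usual care to months 0-12.
2. Label any 24-month cost or outcome contrast as immediate versus delayed mDAS.
3. State that 24-month arm totals do not enter the mDAS-versus-usual-care net costs in the cost-utility projection.

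As a clarification in Section 8.0, Cost and Healthcare Utilization Data, replace the reference to the intervention period with the months since randomisation used in Section 12.0, the same for both arms.

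These are changes of wording and need no new data. The cost is that one planned 24-month ratio is dropped or relabelled.

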### Sustainability

We expect a limited amount of decline in physiologic outcomes with the transition back to usual care. We will test the hypothesis that improvements in A1c, blood pressure, and LDL cholesterol will be maintained during the maintenance time period. The analyses will be conducted similarly as for H1, and will evaluate change in the initial intervention group one year after intervention completion.

Consulting with [name], we will implement a *Sustainability Action Plan (SAP)* to integrate HCs and ensure provision of pharmacy telehealth at an organizational level beyond the period of grant funding. The first phase will identify existing organizational goals and activities that support integration of HCs and pharmacy telehealth approaches into routine clinical operations. Our healthcare system is actively testing HC/peer educator models in multiple locations of the network. In collaboration with these sites and other key stakeholders, we will adapt an existing sustainability checklist to evaluate the presence of specific factors that are needed to support on-going operations within the organization. The next phase involves identifying existing and needed resources within our organization to support delivery of the additional services at the end of the study. The cost-effectiveness data (Aim 3) will help guide this procedure. Working with the Illinois Healthcare Reform Implementation Council and our existing relationship with the Illinois Community Health Worker Advisory Board (see letter of support), we will share details on training and reimbursement for community health workers (aka health coaches) as set forth in the Affordable Care Act and Illinois Bill HB5412 (the board will propose training and certification processes for community health workers and advice legislators). [name] (consultant), as the Global Director of Peers for Progress, is actively involved in legislation to provide peer support service reimbursement and will aid in identifying relevant stakeholders. The final step focuses on executing the outlined action plan.

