**Table 4: RE-AIM Framework for Process Evaluation**

|                       |                                                                                                                                                                                                                                                                                    |
|-----------------------|------------------------------------------------------------------------------------------------------------------------------------------------------------------------------------------------------------------------------------------------------------------------------------|
| Reach          | Identify proportion of eligible population contacted, responded, participated, and excluded. Compare demographics and glycemic levels of eligible UI Health patients and study participants. Are the study participants representative of the clinical population?                 |
| Effectiveness  | Determine change in hemoglobin A1c, blood pressure, and other outcomes (Aim 1). Are there unintended consequences of the intervention (e.g., negative impact on quality of life)?                                                                                                  |
| Adoption       | Conduct semi-structured interviews with randomly selected providers, staff, administrators, and health coaches across participating clinical sites (interview guides to be developed). Assess satisfaction and compare resources, setting, and intervention delivery across sites. |
| Implementation | Measure HC activity including encounters and phone calls completed, videoconferencing, and text messages delivered. Determine subject participation in intervention.                                                                                                               |
| Maintenance    | Implement Sustainability Action Plan (Aim 2). Evaluate change in outcomes one year after completion of the intervention and determine if positive outcomes were maintained. Assess drop-out rates and adverse events experienced.                                                  |

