the continued effects of *mDAS* on outcomes over time. The QALY and utility estimates will be based on the Markov model developed by the Diabetes Cost-effectiveness Group at the CDC (using UKPDS data). Sensitivity analyses will estimate the impact of changes in factors such as age, induced health-care visits, incidence of complications, HC costs, physician time, and discount rates. We will discount both QALYs and costs at 3% per year to maintain equivalent treatment of the measures of costs and effectiveness over time. To compare discounted QALYs, we will integrate the area under the Kaplan-Meier curves for each study condition to obtain mean QALYs. The difference between the two areas will provide the incremental effectiveness from receiving *mDAS*.

The ratio of net costs ( $\Delta$  costs) and net utility ( $\Delta$  utility) will yield the incremental cost utility ratio between the *mDAS* and usual care groups. One-way sensitivity analyses will determine the impact of discount rate (0%-10%) on the cost utility ratio. We will also examine variability associated with the cost-utility ratio using a bootstrapping technique. The bootstrapping results will be presented using the acceptability curve approach. The acceptability curve shows the proportion of samples in which the intervention is considered cost-effective relative to a comparison condition given a maximum amount that a decision maker is willing to pay for the outcome (e.g., \$50,000/QALY). Specifically,  $\text{Net Benefit} = (-1) * (\text{Net Costs}) + (\text{Net Effects}) * (\text{Willingness to pay})$  is calculated and the proportion of samples with mean net benefit greater than zero is plotted across a range of willingness to pay values. If *mDAS* lowers costs and produces more health it will tend to have an acceptability curve over 50% across all levels of willingness to pay.

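### The Aim 3 cost-per-QALY ratio rests on projected continued mDAS, which no participant receives, and is not tied to the post-withdrawal data that the trial collects

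*Protocol*

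**What the plan says.** **Exposure and follow-up.** Section 1.0 of the protocol gives the sequence: "After one year, patients completing the mHealth intervention will be monitored for an additional year while the usual care group receives the mHealth approach". Under Crossover Transition in section 6.1, participants who had mDAS in year 1 "will have the intervention components phased out to assess maintenance". The Sustainability text in section 12.0 states: "We expect a limited amount of decline in physiologic outcomes with the transition back to usual care". The Maintenance row of Table 4 sets the task: "Evaluate change in outcomes one year after completion of the intervention and determine if positive outcomes were maintained".

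**Cost per QALY.** Under Cost and Cost Effectiveness in section 12.0: "Cost per QALY will be determined from projections of continued mHealth involvement and assumptions concerning", followed by "the continued effects of" mDAS on outcomes over time. QALYs and utilities come from an external Markov model. Costs and QALYs are both discounted at 3% per year.

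**Sensitivity analyses.** "Sensitivity analyses will estimate the impact of changes in factors such as age, induced health-care visits, incidence of complications, HC costs", then physician time and discount rates. The discount rate alone is given a range (0% to 10%). A bootstrap and an acceptability curve follow.

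**Other Aim 3 results.** The same text plans cumulative costs over 24 months and an incremental ratio, such as cost per change in A1c, at 12 and 24 months.

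**The concern.** The stated basis of the cost-per-QALY ratio is a programme that goes on. No participant is given one: the arm treated first stops after a year, and the usual care arm starts in year 2 and also has one year. The effect of mDAS beyond a year is therefore assumed, while the quantity a one-year programme needs, namely how much effect survives withdrawal, is observed in one arm and given no stated role in the projection.

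This matters for two reasons. First, the Sustainability text says the Aim 3 data will help guide the step of finding resources to keep the services running. A reader weighing a one-year course of mDAS per patient would find no cost per QALY for it. Second, the assumption is not among the factors named for variation. A bootstrap of trial data will not show uncertainty about persistence unless persistence is itself varied.

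**Working it through.** The protocol gives no cost, QALY gain, time horizon or ratio for this analysis, so there is no figure to reproduce. The check is an illustration of how far the choice of programme moves the ratio.

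**Inputs**
- Discount rate 3% per year: protocol, Cost and Cost Effectiveness.
- Length of mDAS, one year: protocol, sections 1.0 and 6.1.
- Horizon H of 10 years, with 5 and 20 as checks: assumed.
- Yearly retention ρ of the effect after mDAS stops, 0 to 100%: assumed. The protocol expects a limited decline without giving its size.
- Units: programme cost 1 per year; QALY gain 1 per year of full effect. Downstream care costs are ignored.

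**Formulas** (years t = 0, …, H−1)
- Continued programme and effect: cost = gain = Σ 1/1.03^t, so the ratio is 1.00 at any horizon.
- One-year programme: cost = 1; gain = Σ (ρ/1.03)^t = [1 − (ρ/1.03)^H] / [1 − ρ/1.03]; ratio = 1/gain.

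**Results, one-year programme, H = 10**

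| Retention per year | Discounted gain | Ratio relative to continued programme |
|---|---|---|
| 0% | 1.00 | 1.000 |
| 25% | 1.32 | 0.757 |
| 50% | 1.94 | 0.515 |
| 75% | 3.52 | 0.284 |
| 90% | 5.87 | 0.170 |
| 100% | 8.79 | 0.114 |

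Worked lines: at 100%, (1 − 1.03^−10)/(1 − 1/1.03) = 0.2559/0.02913 = 8.79, and 1/8.79 = 0.114. At 50%, (1 − 0.4854^10)/(1 − 0.4854) = 0.9993/0.5146 = 1.94, and 1/1.942 = 0.515.

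**Other horizons.** At full retention the ratio is 0.212 for 5 years and 0.065 for 20. At 50% it is 0.529 and 0.515.

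**Comparison with the range that is prespecified.** Take one year of cost, full retention and 10 years. At a discount rate of 0% the gain is 10 and the ratio 0.100. At 10% the gain is (1 − 1.1^−10)/(1 − 1/1.1) = 6.76 and the ratio 0.148. That is about 1.5-fold, against 1.000/0.114, about 8.8-fold, from retention. In this illustration the range fixed in the protocol covers the smaller driver.

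**Direction.** With cost and effect both continued the ratio is 1.00. A one-year programme is equal to that at zero retention and lower at every other retention. The plan as worded is thus, in this illustration, no more favourable to mDAS than a one-year case.

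**The case against.** Projecting QALYs beyond follow-up with a model is ordinary cost-utility practice, and the protocol labels it openly as projection. It speaks of assumptions about continued effects, not of undiminished effects. The sensitivity list is open, and model inputs may be set in an analysis plan that is not shown. The sustainability work concerns services beyond the grant, so a continuing programme is a scenario someone will want. The decline in year 2 is also measured within one arm, since the usual care arm is then on mDAS; a rate taken from it is not plainly better than a declared assumption.

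Much of this stands. Extrapolation as such is no error, the continued scenario is legitimate, and the uncontrolled fade is a reason not to make a one-year case the only base case. What remains is that the protocol states a basis rather than leaving one open, and that basis is not the programme tested. A lasting service in an organisation also does not mean indefinite mDAS for each patient.

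Four stronger readings are tempting and are not supported:
- *That all of Aim 3 is affected.* The 12- and 24-month ratios come from trial data, and the 12-month one compares one year of mDAS with usual care.
- *That the ratio is biased in favour of mDAS.* That requires effects projected further than costs. Charging one year of cost with full persistence when half the effect is in fact kept each year would understate the ratio 8.79/1.94 = 4.5-fold over 10 years, but no text proposes it. Continued involvement carries programme cost, and costs and QALYs are discounted alike.
- *That the month-24 data are set aside.* The text is silent on whether they inform the assumptions.
- *That health-care costs are cut off at one year.* Section 8.0 counts utilization "during the intervention period", but it also follows participants throughout the study, and section 12.0 accumulates costs over 24 months.

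**Conclusion.** The point holds for the cost-per-QALY ratio only. It is defined for a continued programme that the trial does not deliver, it has no stated link to the month 12 to month 24 course in the arm treated first, and neither persistence of effect nor length of involvement is named for variation.

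The choice can matter a great deal: about 9-fold across the full range of retention over 10 years. That size depends on an assumed horizon and retention, on a constant gain per year of full effect standing in for the Markov model, and on leaving out downstream care costs. It shows sensitivity and does not estimate the trial's ratio. The sign is open. This is an inexpensive improvement worth making; it does not touch the effectiveness analysis.

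**What to change.** In section 12.0, Cost and Cost Effectiveness:

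1. Add a cost-per-QALY case for mDAS as tested: one year of programme cost, an effect path informed by the month 12 and month 24 data of the arm treated first, and the same horizon for costs and QALYs.
2. Report it beside the continued-involvement projection, and label the latter as a scenario.
3. Add two factors to the sensitivity analyses: persistence of effect, from none kept to fully kept, and length of mHealth involvement.
4. Show the fade estimate with a range, and say that it is a within-arm change without a concurrent untreated control.

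The cost is a few sentences and a few extra model runs. No new data are needed, since the physiologic outcomes are already collected at both times. The main drawback is the weakness of the fade estimate, which item 4 makes visible.
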